### Service use and QALYs

Service use (additional to the CBT intervention or Supportive Listening which will both be centrally recorded) by patients in both arms of the trial will be measured using the Client Service Receipt Inventory (CSRI) [51]. This will record health and social service contacts in the six months prior to baseline assessment, and the periods prior to 6- and 12-month follow-up interviews. Time lost from work because of MS-related problems will also be measured.

The EuroQol (EQ-5D) [44], a 5 item composite measure which considers mobility, self-care, usual activities, pain/discomfort and anxiety/depression will be used to assess quality of life. The EQ-5D will be used to generate quality adjusted Life Years (QALYs) [52].

#### Blinding

The trial co-ordinator will administer all quantitative assessment procedures and will be kept blind to the treatment allocation of participants until final follow-up has been completed. The trial co-ordinator will not deal with paperwork that links a participant to their therapy condition, or be present when any discussions revealing this information take place. However, if she becomes aware or suspicious of the treatment condition of any participant she will log this lapse of blinding on the trial database for later consideration in a sensitivity analysis. Either way, as all assessments are by self-report, rather than rated by a member of the research team, influences of observer biases are not expected.

Due to the nature of the interventions it is not possible to blind the principal investigators and nurse-therapists as they will be delivering and supervising the therapy sessions. It is also not possible to blind participants to treatment allocation. However, the trial is set up as comparison of two treatments rather than as a treatment versus control condition. The participant information presents both treatments as a way of assisting adjustment to MS with neither treatment being given preference. During statistical analysis the treatment groups will be assigned a code rather than their name so that the statisticians are unaware what the treatment group code represents.

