#### Baseline questionnaire assessments

Eligible participants will be sent the baseline questionnaire and freepost return envelope together with a copy of their consent form. The schedule of assessments in the baseline questionnaire and subsequent follow-up questionnaires is outlined in Table 1.

**Table 1 T1:** Details and schedule of saMS trial assessment procedures

Measures administered	Baseline (week 0)	Mid-therapy (week 5)	Post-therapy (week 15)	6 month follow-up (week 26)	12 month follow-up (week 52)
Demographics	X	-	-	-	-

Detailed MS questions-(date of diagnosis, time since symptoms started, type of MS, recent and current relapses, treatment for depression, supplements or alternative therapies, participation in MS organizations)	X	-	-	-	-

Brief MS questions (recent changes in medication, interventions, recent and current relapses)	-	-	X	X	X

Expectations/preferences for therapy	X	-	-	-	-

Global improvement and satisfaction ratings	-	-	X	-	-

Feedback on CBT manual/strategies	-	-	X	-	-

Continuation of use of CBT	-	-	-	X	X

General Health Questionnaire (GHQ-12 [41])	X	X	X	X	X

Work and Social Adjustment Scale (WSAS [43])	X	X	X	X	X

Beliefs about Emotions Scale (BES; Rimes & Chalder; in preparation)	X	X	X	X	X

Significant Others Scale (SOS [49])	X	-	X	X	X

Acceptance of Chronic Health Conditions Scale (ACHC [45])	X	X	X	X	X

Psychological Vulnerability Scale (PVS [46])	X	X	X	X	X

Brief Illness Perception Questionnaire (B-IPQ [48])	X	X	X	X	X

Cognitive and Behavioural Responses to Symptoms Questionnaire (CBRSQ; Moss-Morris, Chalder, Skerrett & Baldwin, in preparation)	X	X	X	X	X

Client Service Receipt Inventory (CSRI [51])	X	-	-	X	X

EuroQoL (EQ5D [44])	X	-	-	X	X

Self-report Expanded Disability Status Scale (EDSS [50])	X	-	-	-	X

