#### Outcome assessments

Questionnaires (see Table 1) will be completed at baseline (prior to randomisation), mid-therapy (session 5 of therapy sessions), post-therapy follow-up (15 weeks after randomisation), 6 month follow-up (26 weeks after randomisation) and 12 month follow-up (52 weeks after randomisation). All assessments are questionnaire-based. Data collection will be managed by the trial co-ordinator who will be blind to treatment allocation. Participants will be able to choose whether to complete online or paper-based questionnaires (returned by freepost). Dates that questionnaires are sent out and received will be recorded. A reminder phone call or reminder emails will be used if the questionnaire is not received within two weeks of send-out. After four weeks another copy of the questionnaire pack will be reissued.

If participants are unable to complete questionnaires themselves (e.g. due to relapse) the trial co-ordinator will go through the questionnaire on the telephone and this will be logged as such on the trial database. Spouses/partners/friends will not be allowed to complete the questionnaire on the participant's behalf or assist them with writing their answers. Completed, returned questionnaires will be checked by the trial co-ordinator and participants contacted if there is a large amount of missing data.

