### Data inputting

Data will be input into a flat SPSS spreadsheet by the trial co-ordinator. All primary data (GHQ and WSAS) at all time points will be double entered by an administrator. This will then be checked for errors and discrepancies, which will then be corrected by consulting the raw questionnaire data (paper based or online). A percentage of all other data inputting will also be double entered to ensure accuracy. Any follow-up action (e.g. double entry of more data) will be taken as necessary.

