#### Independent monitoring and quality control

A Trial Steering Committee (TSC) including a Data Monitoring Group has been set up to monitor the conduct of the trial. They will provide overall supervision for the trial and safeguard its integrity. Authority for continuation of the trial lies with the TSC. The committee includes an independent chairperson, the lead and principal investigators, the trial co-ordinator, a statistician, a representative from the MS Society and a patient representative. The committee will meet at least annually during the trial period, and more frequently and/or via telephone conference or email communication if pressing issues arise.

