#### Stopping/discontinuation rules

Departures from the trial protocol, changes to the manualized treatments, and breaking of the randomization code will only occur with the advice of the TSC if it becomes apparent that a particular treatment arm is causing a consistent pattern of deterioration, or if there is another obvious and significant clinical necessity.

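### The trial co-ordinator is said to be blind until final follow-up, but CBT-named items sit in the week 15, 26 and 52 questionnaires that she checks and enters

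*Protocol article*

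**What the plan says.** The Blinding section gives the co-ordinator all quantitative assessment procedures and says she remains unaware of allocation until the last follow-up is complete. It adds that she "will not deal with paperwork that links a participant to their therapy condition, or be present when any discussions revealing this information take place". If she does learn or suspect a participant's arm, she records it, and a sensitivity analysis is to take these lapses into account. The section then argues that observer bias is not expected in any case, because every assessment is self-reported and none is rated by the team. The Discussion repeats that she is blind and lists this among the measures taken against bias.

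The text introducing Table 1 says that the table sets out what the baseline and follow-up questionnaires contain. Two of its rows name one arm's treatment: "Feedback on CBT manual/strategies", marked at week 15, and "Continuation of use of CBT", marked at weeks 26 and 52.

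Under Outcome assessments, "Completed, returned questionnaires will be checked by the trial co-ordinator and participants contacted if there is a large amount of missing data". Where a participant cannot complete the form alone, "the trial co-ordinator will go through the questionnaire on the telephone". Under Data inputting, "Data will be input into a flat SPSS spreadsheet by the trial co-ordinator".

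**The concern.** The promise that she handles no paperwork linking a participant to a therapy conflicts with the content of the paperwork she is assigned. Participants, nurse-therapists and principal investigators all know the allocation, so the co-ordinator is the main blinded person in contact with participants during outcome collection. If her blinding is lost before the 12-month primary assessment, the trial cannot accurately report that outcomes were collected blind. The planned check on lapses would also have few clearly unexposed participants to compare with the exposed ones.

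**Working it through.** No power, alpha or effect-size arithmetic applies. The check is to set the sections side by side.

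**1. When the items appear.** Table 1 has four post-baseline time points: weeks 5, 15, 26 and 52. CBT-named items are marked at weeks 15, 26 and 52, which is 3 of 4. Week 5 has none, so exposure through this route starts at week 15. The Abstract places the primary outcomes at twelve months, so two questionnaires with CBT-named items come before the primary one, and the primary one contains such an item as well.

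**2. Whom the items concern.** The Trial interventions section says each participant is issued one manual, for CBT or for SL. A question about the CBT manual, or about continuing to use CBT, therefore has content only for the CBT arm. The article does not say who is sent these items; this step rests on their titles and on the single-manual rule.

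**3. Who handles them.** The co-ordinator administers (Blinding), checks and follows up gaps (Outcome assessments) and enters data (Data inputting). No separate route for the CBT-named items is described.

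**4. What she would see.**
- *Items sent only to the CBT arm:* the make-up of the questionnaire shows the arm, and whoever sends it must know the arm beforehand.
- *Items sent to everyone:* a completed section points to CBT. A blank or not-applicable section suggests SL, but less surely, because a CBT participant may skip it.

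In either case allocation becomes known or strongly suspected for many or most participants who return a week 15 questionnaire. The number depends on distribution and completion, which the article does not give.

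**5. The lapse log.** Both knowledge and suspicion are to be logged. With exposure built into the schedule, a log kept as instructed would cover a large share of participants. A sensitivity analysis designed for occasional lapses would then have a small and selected comparison group.

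**6. Whether self-report removes the consequence.** Largely, but with two stated exceptions. Telephone completion with the co-ordinator can include GHQ and WSAS. And the section on moderators says that she reviews and scores the self-report EDSS, which Table 1 schedules at baseline and week 52. The neurologist's co-scoring reduces the risk, but the Blinding section's statement that nothing is rated by the team is not strictly true. The EDSS is a measure of progression, and the Statistical analysis plan section intends to examine whether patients with marked progression unduly influenced the results.

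**The case against.** The strongest reply is that little follows for the primary result. GHQ and WSAS are normally completed by participants who know their own treatment. That is the larger source of possible bias, and masking the co-ordinator does not touch it. All GHQ and WSAS data are double entered and discrepancies resolved against the raw questionnaires. Telephone completion is limited to participants unable to complete the form and is logged. Contact about gaps is limited to large amounts of missing data. The EDSS is neither a primary nor a listed secondary outcome. The article also foresees lapses, and a fuller protocol might contain a separate return route. All of this stands as a limit on the size of the problem. It does not reconcile the sections: the article places these items in questionnaires it assigns to her while stating that she sees nothing of the kind.

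Three stronger readings are tempting and are not supported.

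- *The steering committee unblinds her.* The committee includes "the lead and principal investigators, the trial co-ordinator, a statistician" and advises on changes "if it becomes apparent that a particular treatment arm is causing a consistent pattern of deterioration". But the Blinding section already bars her from discussions that reveal allocation, the membership of the Data Monitoring Group is not given, and arm-level or coded summaries need not identify individuals.
- *The statisticians' group code is revealed by CBT-only columns.* No section says that their analysis file contains those columns.
- *All 122 participants are identifiable.* This ignores the planned attrition of around 10%, and a blank section is ambiguous if the items go to everyone.

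**Conclusion.** The contradiction is real and confined to the questionnaire route. As written, the co-ordinator's blinding is not secured by the design from week 15 onward, and exposure is likely for many or most participants before the 12-month assessment. This assumes that the CBT-named items apply only to CBT participants and that no undisclosed route keeps them away from her. The documents give no basis for quantifying bias in GHQ or WSAS. It is probably small, with telephone completion as the remaining direct path. What is clearly affected is the accuracy of the blinding claim, the usefulness of the lapse-based sensitivity analysis, and the unqualified statement that the team rates no assessment. The point is worth correcting because the Discussion relies on this safeguard and restoring it is nearly free.

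**What to change.** Choose one of two routes.

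1. **Arm-neutral items for all participants**, for example *feedback on your therapy manual* and *continued use of what you learned*. Closed response options are safer, since free text could name CBT techniques. The cost is rewording two items and losing some CBT-specific detail.
2. **A separate form**, returned to and entered by the administrator who already does the double entry, and withheld from the co-ordinator until final follow-up is complete. It should be dispatched by someone other than the co-ordinator or sent to everyone, and the online version needs the same separation. If a questionnaire is completed by telephone, someone else should cover this form. The cost is one extra return route using existing staff.

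Under either route, amend the Blinding section to acknowledge telephone completion and the co-ordinator's scoring of the EDSS. For any questionnaires with CBT-named items that have already been returned, log the exposure and report it.

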#### Informing the participants' health professionals regarding involvement in the trial

After the first session, the nurse-therapist will write to the participant's GP and MS service to inform them of the patient's participation in the trial. For CBT patients this will also include a summary of the assessment made and the areas that are likely to be concentrated on in the remaining sessions (discussed and agreed with the participant and a copy sent to the participant for their own records).

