#### Moderators of Treatment Improvement

We will also look at two potential moderators of patients' response to treatment, the therapeutic alliance and perceived social support.

The therapeutic alliance is measured using the Alliance subscale of the Therapy Competence and Fidelity Rating scale [34]. Independent raters blind to treatment outcome will use this scale to rate therapy tapes from each of the two therapists. The scale includes items including emotional expression by the patient and level of empathy expressed by the therapist. Items are rated on a 7-point Likert Rating Scale, with anchors at four points along the scale [e.g. 'not at all' (1), 'somewhat' (3), 'considerably' (5) and 'extensively'].

Social support is measured by the Significant Other Scale (SOS) [49]. We are using a shortened version of this scale (8 items) where the participant is asked to state one key support person and then rate desired and received support in different domains (e.g. practical help and socialising).

In addition to these measures we have included a number of questions to measure illness severity, progression and relapse (see Table 1) including the self-reported Expanded Disability Status Scale (EDSS)[50]. This will allow us to assess whether there has been any noticeable disease progression. The self-reported EDSS is a relatively new instrument which allows MS patients to self-report their current disease status, rather than this being assessed by a neurologist during a clinical examination. The questionnaire includes items which relate to mobility, strength, co-ordination, sensation, bladder, vision, speech, swallowing, and cognition. Using the responses from these items, functional system scores are computed and an EDSS score is assigned to the participant ranging from 0 (no neurological impairment) to 10 (death from MS). The trial co-ordinator will review and score each questionnaire, which is then co-scored by a neurologist specialising in MS in order to ensure reliability of scoring.

Patients will also be asked to rate their treatment preference at the beginning of the trial and their feelings about treatment efficacy at the end of the trial.

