#### Statistical analysis plan

Statistical analysis will be carried out in SPSS and/or Stata general purpose statistical analysis packages. Mediation modeling may require use of specialist structural equation modeling software (e.g. AMOS or M-Plus).

All treatment group comparisons will be carried out on an intention-to-treat basis, that is subjects will be analyzed in the group to which they were randomized irrespectively of the treatment received. The primary and secondary longitudinal outcomes will be analyzed using linear mixed modeling. In these models the outcome variable at the post-treatment time points will be the dependent variable and baseline values of the outcome variable, centre, time (post-treatment, 6 M follow-up or 12 M follow-up), group (CBT or Supportive Listening) and a time × group interaction terms will feature as explanatory variables. To account for correlation between measures taken on the same individual at various time points subject-varying random intercepts and slopes of time will also be included in the model. Further baseline variables might be used as explanatory variables, to provide more powerful group comparisons if they are found to be predictive of the outcome variable. As the model fitting will by maximum likelihood such analyses are valid if missing data arises at random (MAR). The effect of informative missingness processes will be explored by means of a formal sensitivity analysis [54].

We will further investigate whether results were unduly influenced by patients who have shown marked disease progression during the trial or who have altered medication during the trial period. We will also assess the sensitivity of the results to excluding patients who did not receive a sufficient number of treatment sessions or those who had low expectations of the therapy they received.

An approach similar to Baron and Kenny's mediation modeling [55]will be used to explore whether change of psychological outcomes mediates the path from therapy to change in MS adjustment. Specifically we will use instrumental variable methods advocated by Dunn and colleagues to try and adjust for unobserved confounders of the path from mediations to outcomes [56,57].

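### The Blinding section's claim that no assessment is rated by the research team is not true of the EDSS, which the co-ordinator scores from a week-52 pack that can show her the arm and the primary outcomes

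*Protocol article*

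**What the plan says.** The Blinding section keeps the trial co-ordinator unaware of allocation until final follow-up is complete. It bars her from paperwork and discussions that would reveal the arm, and has her log any lapse for a sensitivity analysis. It then argues that a lapse would do no harm either way: "as all assessments are by self-report, rather than rated by a member of the research team, influences of observer biases are not expected".

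The section on moderators of treatment improvement describes the self-reported EDSS. Functional system scores are derived from the participant's answers and an EDSS score from 0 to 10 is given. On who does this, it says: "The trial co-ordinator will review and score each questionnaire, which is then co-scored by a neurologist specialising in MS". The stated purpose of the measure is to detect disease progression.

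Table 1 schedules the EDSS at baseline and week 52 only. At week 52 it also schedules the GHQ, the WSAS and an item on continued use of CBT. Under Outcome assessments the co-ordinator checks returned questionnaires, and where a participant cannot complete one, "the trial co-ordinator will go through the questionnaire on the telephone". Under Data inputting she enters the data.

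The statistical analysis section will examine whether the results were unduly influenced by "patients who have shown marked disease progression during the trial".

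**The concern.** The sentence in the Blinding section is the article's stated reason why an unblinded co-ordinator would not bias any assessment. If one measure is graded by the team, that reason fails for that measure, and its grading needs its own protection.

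The measure concerned bears on a planned robustness check. Suppose a scorer who can see a poor week-52 WSAS or GHQ, or signs of the arm, is more ready to grade a participant as worse. Membership of the progressed group would then depend partly on the outcome that the check is meant to test. The check could make the primary result look either sturdier or more fragile than it is.

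**Working it through.** No arithmetic applies. The question is who assigns the score, what that person can see, and where the score is used.

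1. **Is any assessment rated by the research team?** The Blinding section says none is. The moderators section has the co-ordinator score every EDSS questionnaire. She is plainly part of the research team: she screens, administers all quantitative assessments and enters data. The answers are self-reported, but the grade is not. The form is also "co-scored by a neurologist specialising in MS in order to ensure reliability of scoring", which implies that two scorers could differ and so that some judgement is involved. The two sections conflict on this measure.

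2. **Is the first scorer masked to arm?** By intention, yes: Blinding and Outcome assessments both say so. But the week-52 column of Table 1 contains both the follow-up EDSS and the item on continued use of CBT. Table 1 does not say whether that item goes to everyone. If only CBT participants receive it, its presence shows the arm. If all receive it, the answers are likely to. The feedback item on the CBT manual at week 15 raises the same issue earlier. No section says these items are kept from the co-ordinator, and she checks and enters the questionnaires. Following the plan as written can therefore defeat the masking it intends.

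3. **Is the first scorer masked to the primary outcomes?** Nothing says so. GHQ and WSAS share the week-52 assessment with the EDSS, and she handles all three. For a questionnaire completed by telephone she hears every answer. The same section does specify raters blind to treatment outcome for the therapeutic alliance scale, so the article states this safeguard for one rated measure and not for the other.

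4. **Is the second scorer masked?** The article does not say.

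5. **Where does the score go?** The EDSS is not among the primary or secondary outcomes. Its purpose is to show progression, and progression enters the statistical analysis section as a check on undue influence. With only two EDSS time points, any EDSS change during the trial rests on the single week-52 grade, the one made alongside the CBT item, GHQ and WSAS.

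**The case against.** The strongest reply is that the EDSS here really is self-report. The article says that it "allows MS patients to self-report their current disease status, rather than this being assessed by a neurologist during a clinical examination". The answers are fixed before anyone scores them, scoring follows from those answers, and a second scorer is a safeguard. The Discussion describes the assessments of patient outcomes as self-reported, and the EDSS is not one of those outcomes, so the wording in Blinding may only be loose. This stands in part: it limits how far a scorer could move a grade, and it confirms that GHQ and WSAS are not affected. It does not rescue the sentence, which covers all assessments and is used to dismiss the effect of a blinding lapse.

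A second reply is that lapses are already logged for a sensitivity analysis. That helps if the co-ordinator notices and records each one. It does not cover sight of GHQ and WSAS, which is not a lapse of allocation blinding.

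A reader might go further and infer that the EDSS is scored with no masking at all. The documents do not support that. The co-ordinator is expressly to be kept blind to allocation, and for the neurologist the article is silent, which a condensed article may be. A reader might also infer that the neurologist learns the arm because "the nurse-therapist will write to the participant's GP and MS service to inform them of the patient's participation in the trial", and the letter carries extra content for CBT patients. No section says that the co-scoring neurologist works in a recruiting service or receives those letters, so this is conjecture and forms no part of the point.

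**Conclusion.** The point holds as an inconsistency with a small practical consequence. The statement in Blinding is not true of the EDSS, and the week-52 schedule lets the arm and the primary outcomes be visible to its first scorer despite the intended blinding.

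The consequence is limited to the check on marked disease progression. The primary analysis of GHQ and WSAS is unaffected. No size can be put on the effect: the documents give no progression rate or misgrading rate, and do not say how the check will be carried out or how much weight the EDSS has beside the questions on severity and relapse. Any figure would rest wholly on invented inputs.

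The conclusion assumes that the co-ordinator scores the EDSS from the same questionnaires that she checks and enters, and that the CBT-use item is not withheld from her. The article supports the first and says nothing against the second. This is a cheap improvement and does not threaten the trial's main conclusion.

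**What to change.** In the moderators section, state that both scorers grade EDSS pages separated from the rest of the pack and identified by code only, without sight of the CBT-use items, GHQ, WSAS or arm. Someone other than the co-ordinator should do the separating before she checks the rest; the administrator already named for double entry is one option. For online questionnaires the EDSS items can be exported alone. Where the co-ordinator has taken a questionnaire by telephone, separation cannot undo what she has heard, but the neurologist's score is still protected.

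In the Blinding section, limit the sentence to the self-completed questionnaire outcomes and name the EDSS as an exception.

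The cost is two short wording changes and a little clerical work. Both scorers are already planned, so no new staff are needed.
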